## Abstract

**Background:**

Frailty is common in older age and is characterised by loss of biological reserves across multiple organ systems. These changes associated with frailty mean older people can be vulnerable to sudden, dramatic changes in health because of relatively small problems. Older people with frailty are at increased risk of adverse outcomes including disability, hospitalisation, and care home admission, with associated reduction in quality of life and increased NHS and social care costs. Personalised Care Planning offers an anticipatory, preventative approach to supporting older adults to live independently for longer, but it has not been robustly evaluated in a population of older adults with frailty.

**Methods:**

Following an initial feasibility study, this multi-centre, individually randomised controlled trial aims to establish whether personalised care planning for older people improves health-related quality of life. It will recruit 1337 participants from general practices across Yorkshire and Humber and Mid-Mersey in the North of England. Eligible patients will be aged 65 and over with an electronic frailty index score of 0.21 or above, living in their own homes, without severe cognitive impairment and not in receipt of end-of-life care. Following confirmation of eligibility, informed consent and baseline data collection, participants will be individually randomised to the PeRsOnaliSed care Planning for oldER people with frailty (PROSPER) intervention or usual care in a 2.6:1 allocation ratio. Participants will not be blinded to allocation, but data collection and analysis will be blinded. The intervention will be delivered over 12 weeks by a Personal Independence Co-ordinator worker based within a voluntary sector organisation, Age UK. The primary outcomes are health-related quality of life, measured using both the physical and mental components of the Short-Form 12 Item Health Questionnaire at 12 months after randomisation. Secondary outcomes comprise activities of daily living, self-management capabilities and loneliness, admission to care homes, hospitalisations, and health and social care resource use at 12 months post randomisation. Parallel cost-effectiveness and process evaluations will be conducted alongside the trial.

**Discussion:**

The PROSPER study will evaluate the effectiveness and cost-effectiveness of a personalised care planning approach for older people with frailty and inform the process of its implementation.

**Trial registration:**

ISRCTN16123291.  Registered on  28 August 2020.

**Supplementary Information:**

The online version contains supplementary material available at 10.1186/s13063-023-07857-1.

## Background and rationale

Frailty is a condition characterised by reduced biological reserves and increased vulnerability to adverse outcomes [1]. Frailty is considered more readily reversible at early stages than disability and has higher predictive value than chronic disease for adverse outcomes. Single disease management frameworks are less relevant for older people living with frailty and best practice suggests that care for older people with frailty should be proactive and person-centred, responsive to personal experiences of illness, individual priorities, and predicaments [1, 2].

Personalised Care Planning (PCP) is an anticipatory, negotiated series of guided conversations between a patient and a suitably trained individual [3] and presents a promising way to achieve a shift towards proactive, person-centred care in frailty [2–4]. PCP moves away from a focus on individual disease management and a reactive crisis-driven response in healthcare. Shared decision making is the central mechanism in PCP involving collaborative discussions between patients and practitioners, goal setting, and agreement of an action plan. This process enables linkage to additional mechanisms for improving outcomes through more effective self-management, better care coordination, and better access to community resources (social support). It includes creating a care plan and monitoring delivery through regular follow-up. Key outcomes are improved physical and mental health, self-management capabilities, health-related behaviours, and changes in health service use [3].

Social cognitive theory (SCT) is the theoretical model that resonates most with the tenets of PCP in the context of frailty and provides the underpinning theory for developing and optimising our planned intervention [5]. SCT specifies factors governing the acquisition of competencies that can profoundly affect physical and emotional wellbeing [6]. It identifies knowledge, skills, self-efficacy, outcome expectations, goals, and concrete plans, as well as the perceived social and environmental facilitators and impediments as core determinants influencing our health habits. Social and environmental factors are of core importance for maintaining quality of life in older age and are therefore highly relevant for optimising PCP for older people with frailty.

Although a 2015 Cochrane review identified that PCP for long-term conditions (LTCs) can improve physical and mental health, and self-management capability, the majority of the 16 studies summarised were focused on single LTCs such as diabetes [3]. None of the studies selected participants based on frailty. Furthermore, a comprehensive evaluation of PCP in the UK has identified widespread, poor implementation [7, 8].

In England, the 2019 National Health Service (NHS) Long Term Plan set out key ambitions for the health service over the next 10 years [9]. The Plan included a focus on enabling older people living with frailty to live independently at home for longer. This was to be achieved via primary care-based multidisciplinary teams providing tailored support. Any intervention therefore must be sufficiently robust and flexible to integrate with commissioning and provider organisations.

In 2013 Age UK—the largest voluntary sector organisation providing support and services to older adults in the UK—developed an Integrated Personalised Care Planning (IPCP) service, working across commissioning and provider organisations [10]. We collaborated with the Age UK IPCP service to develop our PROSPER (Personalised Care Planning for Older People) intervention—designed to improve quality of life for older people with frailty and reduce use of health and social care services.

The trial methods, fidelity, and implementation were tested in a feasibility study in 2019 [11] and subsequent adjustments made to both the trial design and intervention delivery. Here we describe the protocol for the definitive trial evaluation of PROSPER compared with usual care (UC) to evaluate its effectiveness in improving quality of life (QoL) for older people with frailty.

## Aim and objectives

This trial aims to evaluate the clinical and cost-effectiveness of PCP for older people with frailty, compared with UC alone.

The primary objective is to establish whether PCP for older people with frailty improves health-related quality of life (HRQoL), measured using either the Physical Component Summary (PCS) or the Mental Component Summary (MCS) of the Short-Form 12-Item Health Questionnaire (SF12) at 12 months after randomisation.

Secondary objectives are to establish:Whether PCP improves activities of daily living at 12 months post-randomisation.Whether PCP improves self-management capabilities and loneliness 12 months post-randomisation.Whether PCP reduces admission to care homes at 12 months post-randomisation.Whether PCP reduces hospitalisations, overall health, and social care resource use at 12 months post-randomisation.The cost-effectiveness of PCP.The process of implementation within participating sites and determine how PCP should be implemented more broadly across the wider NHS.

## Methods

### Trial design

PROSPER is a pragmatic, multi-centre, randomised controlled trial (RCT) with a two-level partially nested hierarchical design, comparing PCP versus UC in older people with frailty. The previous cluster randomised feasibility trial indicated that PCP was being individually tailored by Personal Independence Coordinator (PIC) workers in partnership with older people, with limited involvement of the primary care clinical team, minimising risks of intervention contamination. This aligns with the overall aim and theoretical underpinnings of PROSPER to direct a shift away from a medical model of care in frailty towards a more socially orientated model reflecting how the intervention would likely be implemented in practice. Considering this information, we have changed the unit of randomisation from a cluster to an individually randomised controlled trial. The change in trial design will also help mitigate some of the challenges faced during recruitment in the feasibility study, allowing further detail about the intervention to be provided up-front, with the potential advantage of minimising the number of participants who subsequently decline participation in the early stages of the intervention. Additional benefits include smaller overall sample size and less constraint in terms of recruiting larger numbers from individual practices.

This study will also comprise a mixed method embedded process evaluation and Study Within a Trial (SWAT). These will be reported separately.

### Study setting

Participants will be recruited from general practices within four geographic localities in the relatively rural Northwest of England (Mid-Mersey region) and a large area of conurbation in West Yorkshire (Leeds, Bradford, Wakefield).

### General practice recruitment and eligibility

A range of approaches will be used to engage with general practices including local National Institute for Health Research (NIHR) Clinical Research Networks (CRNs), professional networks, and practices listed on the Office for Health Improvement and Disparities (OHID) website [12]. General practice eligibility will be based on the following:Having completed a Site Feasibility Assessment Questionnaire (SFQ), followed by a meeting.Provided confirmation of capacity and capability (C&C).Using either SystmOne or Egton Medical Information Systems (EMIS) for patient electronic health records (EHRs).Having identified a member of staff with a clinical interest in older people or frailty to act as a ‘champion’.Allowing research staff with appropriate permissions to access participant EHRs.Being willing to make reminder calls/send SMS reminders to patients who do not respond to an invitation letter.Located within the geographical footprint of our voluntary sector (Age UK) delivery teams.Willing to engage with intervention delivery staff from Age UK.Assigning a practice ‘buddy’ to the Age UK team for administrative purposes.Providing an honorary contract for Age UK delivery team to allow access to EHRs of study participants.

Practices that provide an existing or planned PCP service targeting older people with frailty that significantly overlaps with the PROSPER intervention model will be excluded.

### Participant identification and eligibility

Potential participants will be identified by practice staff electronically screening for the inclusion/exclusion criteria within patient EHRs. Templates to assist with searches will be available for the two most used EHR systems, EMIS and SystmOne.

#### Inclusion criteria

We undertook initial statistical and health economic modelling work to inform how PCP should be targeted, based on the relationship between frailty (measured using the electronic frailty index (eFI)), health and social care use, and health-related quality of life, using existing secondary data sources [13, 14]. Patients meeting *all* the following criteria (and none of the exclusion criteria) will be eligible for inclusion:Frailty defined by eFI range ≥0.21 (EHR screen)Aged 65 or over (EHR screen)Willing and able to give informed consent (or has a personal consultee declaration if the patient lacks capacity; assessed at baseline visit)

#### Exclusion criteria

Patients meeting *any* of the following criteria will not be eligible for inclusion, assessed at screening:Resident of a care home (EHR screen).Registered on Gold Standards Framework, indicating an individual is likely to be in the last year of life (GSF; EHR screen).Deemed inappropriate to approach for safety reasons (GP/Advanced Nurse Practitioner (ANP) screen).Severe cognitive impairment, as participants must be able to engage with goal setting and action planning, defined as a Blind Montreal Cognitive Assessment (MoCA) score of <7 assessed at telephone registration, or full MoCA score <10, assessed face-to-face at baseline visit due to mental capacity concerns.Member of household currently or previously consented to take part in this study (assessed at registration).In receipt of another PCP service for older people (assessed at registration).

Eligibility waivers to participant inclusion/exclusion criteria are not permitted. The number of eligible participants and the number of potential participants removed, along with the reason will be logged by the University of Leeds Clinical Trials Research Unit (UoL CTRU) where possible. Practices will provide an anonymised list of the gender, age, eFI, ethnicity, and invitation number to allow comparison of the characteristics of those declining to participate to those entering the trial. This information will support discussion of generalisability of study results in accordance with CONSORT reporting guidelines [15]. Participant eligibility lists will be generated once. However, if the response rate is low, potential participants will be re-approached 3–6 months after their first invitation after the lists have been reviewed and any potential participant who has left the practice or died in the interim removed.

### Recruitment

An information pack will be sent out by the practice staff to all those on the eligibility list in batches, if necessary. The pack will include:An invitation letter for the participantAn information sheet for the participantAn invitation reply formA pre-paid envelope

The information provided will summarise the study and ask if the potential participant would be willing to consider participation in the study. The information will state potential participants will be contacted by the study team if no response is received within 7 days. Practices may also send a single SMS text reminder.

Contact details for the research team will be provided should the potential participant require more information before committing to the study. In addition, this can be indicated on the enclosed reply form. The completed reply form (including an option to decline, with or without noting a reason) can be returned directly to the research team using a pre-paid envelope or alternatively potential participants or consultees can respond via telephone, email, or request a return call via SMS.

It may not be clear at the time of approach whether the potential participant lacks capacity to consent for themselves so information that can be given to a potential personal consultee will be available at the consent/baseline visit.

The above process will be repeated until the recruitment target is met. Reasons for decline will be documented when available. Study materials will be re-sent if requested, but no further calls will be made unless specifically requested by the patient.

### Trial consent, assent, and randomisation

A researcher trained in Good Clinical Practice (GCP) and with an appropriate level of Disclosure Barring Service (DBS) check, will initially telephone potential participants who have returned an expression of interest (EOI) from the study invitation. *Verbal* consent will be obtained over the telephone. Final eligibility checks will be done, and the potential participant’s details will be collected (practice name, date of birth) so they can be registered onto the study. Following registration, the researcher will arrange a visit to the potential participant’s home to discuss the study further, obtain *written* informed consent, confirm eligibility, and collect baseline data. Brief information about the process evaluation and SWAT will be given at this time but these will have separate recruitment, randomisation, and consent procedures.

A lack of capacity to consent is not a basis for exclusion. If a researcher has concerns about capacity of the potential participant to provide verbal consent, they will arrange a home visit to undertake a capacity assessment in line with the Mental Capacity Act (2005) guidance [16]. At this time, a consultee will be identified, and advice sought, if necessary. The MoCA test will be administered separately. Participants who record a MoCA score of <10 face-to-face will be excluded from the study, as they are unlikely to be able to engage in meaningful shared decision making with the PIC. Baseline data will not be collected for those who are ineligible. Research staff will also ascertain whether a face-to-face visit or telephone support will be needed for follow-up at the baseline visit.

#### Consent

The right to decline consent to participate in the study, or withdraw from the study, without providing a reason, at any time will be respected. Reasons for declining participation and withdrawals will be noted, if provided.

#### Potentially vulnerable adults

Researchers will review capacity as previously described and involve friends and family as ‘chaperones’ when requested. Where individuals have specific impairments such as sight or hearing loss, the research staff will take measures to mitigate these, such as assisted completion, visual prompts, and use of the Blind MoCA. Research staff will consider participant fatigue during data collection and offer additional visits, if required.

#### Safeguarding of adults

All research staff will receive training in recognising and responding to abuse and will follow their organisational safeguarding procedures to escalate incidents via their individual line managers. In addition, GPs will be notified by the CTRU if a participant’s Geriatric Depression Score (GDS) score at baseline or follow-up indicates possible depression.

#### Randomisation

Participants will be allocated to the treatment groups using the CTRU automated randomisation service. Individuals will be randomised with a 2.6:1 ratio (PROSPER intervention: usual care) using minimisation incorporating a random element, stratified by eFI, Nottingham Extended Activities of Daily Living (NEADL) score, GDS score, living arrangements, and practice deprivation index. All randomised participants will be informed of which trial arm they are allocated to via a letter from the CTRU. PICs will be notified of participants randomised to the intervention arm and will make contact to offer the PROSPER intervention. Researchers collecting baseline and follow-up data will be blinded to participant allocation. The process for recruitment and randomisation is outlined in Fig. 1.

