### The PROSPER intervention

The PROSPER intervention was co-produced with our Intervention development Group, comprised six lay people and six primary care professionals. The PROSPER intervention will be delivered by a paid PIC worker. It is anticipated that the delivery teams will comprise 2.0 whole time equivalent (WTE) PIC workers, and 0.5 WTE team leader per geographical area. Wherever possible, delivery teams will work exclusively with an individual practice to maintain continuity.

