### Sample size

One thousand three hundred thirty-seven participants (371 control arm, 966 intervention arm) provides 90% power at the 2.5% significance level (overall Type I error 5%) to detect an effect size of 0.30 in the primary outcomes of SF12 PCS and SF12 MCS scores (consistent with a minimum clinically important difference of 3 points and variance estimates based on published estimates for this population [22] and the unpublished results from our feasibility study). This accounts for 25% losses to follow-up and clustering by PICs in the intervention arm (15 PICs, 50 participants/PIC, 0.03 intraclass correlation coefficient (ICC), 0.30 variation in cluster size). Based on estimates of those 65+ years meeting eligibility criteria (20%), and those providing consent (20%), we anticipate that on average 60 participants will be recruited per practice.

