### Statistical methods

#### Primary outcome analysis

PCP is designed to generate intervention effects on either mental or physical health-related quality of life, or both, depending on an individual’s personal circumstances. Social cognitive theory specifies factors that can profoundly affect both physical and mental health, so our decision to use the SF36 PCS and MCS as the co-primary outcome is closely aligned with our underpinning intervention theory [6] and logic model. Co-primary outcomes will therefore be the physical component summary (PCS) and mental component summary (MCS) scores of the SF12 as a measure of HRQoL at 12 months. Each primary outcome can, independently, characterise a clinically meaningful benefit of the intervention. The intervention will be considered effective if an improvement in either of the summary measures is demonstrated.

The primary analysis will compare mean PCS and MCS scores at 12 months between trial arms using partially nested mixed-effects linear regression models to account for clustering of outcomes in the intervention arm due to the PIC effects [23]. The models will be adjusted for the stratified design factors and participant level covariates expected a priori to be associated with the outcome of interest. The analysis will be undertaken on the intention to treat (ITT) population, which includes all randomised participants in their allocated treatment group, regardless of their level of treatment adherence. Estimated mean difference will be reported with 97.5% confidence intervals and p-values, together with unadjusted and adjusted ICC estimates. Model diagnostics will be used to check that the underlying assumptions are not violated in the analysis. We will explore missing data patterns and reasons for missingness to guide the assumptions around missing data. If it can be assumed data are missing at random (MAR) the primary Intention to Treat (ITT) analysis will use multiple imputation, enabling us to include all randomised participants in the primary ITT analysis. If the data cannot be assumed MAR, we will explore the use of other more complex methods for the primary analysis taking account of data missing not at random (MNAR), such as pattern mixture modelling.

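### The primary model does not name recruiting locality, although PICs are organised by area: adding it as a fixed effect for both arms is a nearly free safeguard for precision and for the PIC ICC

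*Protocol article*

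**What the plan says.** Study setting places recruitment in "four geographic localities in the relatively rural Northwest of England (Mid-Mersey region) and a large area of conurbation in West Yorkshire", the latter made up of Leeds, Bradford and Wakefield. With Mid-Mersey these are the four localities. The section on the PROSPER intervention expects "2.0 whole time equivalent (WTE) PIC workers, and 0.5 WTE team leader per geographical area", with each team working with a single practice where that can be arranged. A PIC (Personal Independence Coordinator) is therefore tied to an area, and so to one locality.

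Under Randomisation, allocation is by minimisation, "stratified by eFI, Nottingham Extended Activities of Daily Living (NEADL) score, GDS score, living arrangements, and practice deprivation index". Under Primary outcome analysis, PCS and MCS at 12 months are compared by partially nested mixed models with a PIC effect in the intervention arm. On covariates the section says: "The models will be adjusted for the stratified design factors and participant level covariates expected a priori to be associated with the outcome". The participant-level covariates are not listed. Unadjusted and adjusted ICCs are both to be reported, and the continuous secondary outcomes follow the same method.

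**The concern.** Randomisation is individual, so both arms draw on the localities in about the same proportions. A locality difference in SF12 that both arms share nearly cancels from the treatment contrast, but the stated model has no named term that lets it use this. In the intervention arm, PICs in different localities differ partly because the localities differ, and the PIC random effect takes up that variation. The control arm has no such effect, so there the same variation stays in the residual.

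The model then counts as uncertainty about the treatment effect something that the design has already balanced. At stake are the width of the intervals for both co-primary comparisons and the meaning of the reported ICC, which would mix area and PIC.

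**Working it through.** **1. The plan's own figure.** The Sample size section says the design "provides 90% power at the 2.5% significance level (overall Type I error 5%) to detect an effect size of 0.30", with 371 control and 966 intervention participants, 25% losses, and "15 PICs, 50 participants/PIC, 0.03 intraclass correlation coefficient (ICC), 0.30 variation in cluster size". Only the intervention arm carries a design effect:

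DE = 1 + ((1 + 0.30²) × 50 − 1) × 0.03 = 1 + 53.5 × 0.03 = 2.605

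Control n = (1 + 2.605/2.6) × ((2.241 + 1.282)/0.30)² = 276.1. Dividing by 0.75 gives 368, the intervention arm is 2.6 times that (957), and the total is 1325 against the stated 1337.

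With 371 × 0.75 = 278.25 and 966 × 0.75 = 724.5 analysed, SE = √(1/278.25 + 2.605/724.5) = 0.0848, and power = Φ(0.30/0.0848 − 2.241) = 90.3%. The figure reproduces, taking the 2.5% as two-sided.

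**2. How much locality variance reaches the PIC term.** Assume the 15 PICs split 4/4/4/3 over the localities. Of 105 pairs of PICs, 6 + 6 + 6 + 3 = 21 share a locality and 84 do not, so about 84/105 = 0.8 of the locality variance appears as PIC variance. A less even split such as 6/3/3/3 gives 81/105 = 0.77.

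**3. Effect on the standard error.** Let λ be the share of total variance lying between localities after adjustment. The article gives no value, so a range is assumed. The ICC seen by the model is 0.03 + 0.8λ. For λ = 0.01 it is 0.038, so DE = 1 + 53.5 × 0.038 = 3.033, SE = √(1/278.25 + 3.033/724.5) = 0.0882, and the ratio to 0.0848 is 1.04.

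**4. Simulation.** There were 2000 trials per row: 15 PICs split as above, PIC ICC 0.03, cluster-size variation 0.30, true effect 0.30, locality not used in allocation, REML fits, no covariates. Paired entries are without / with locality as a fixed effect.

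| λ | Analytic SE ratio | Model SE | Width ratio | Mean ICC | Power |
|---|---|---|---|---|---|
| 0 | 1.00 | 0.0832 / 0.0834 | 1.00 | 0.030 / 0.030 | 91.4% / 90.9% |
| 0.005 | 1.02 | 0.0851 / 0.0837 | 1.02 | 0.034 / 0.030 | 90.4% / 91.3% |
| 0.01 | 1.04 | 0.0865 / 0.0836 | 1.03 | 0.038 / 0.030 | 90.7% / 91.8% |
| 0.02 | 1.08 | 0.0896 / 0.0840 | 1.07 | 0.044 / 0.031 | 87.0% / 89.7% |
| 0.05 | 1.19 | 0.0983 / 0.0838 | 1.17 | 0.065 / 0.030 | 81.6% / 91.4% |

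The Monte Carlo error of a power figure is about √(0.9 × 0.1/2000) = 0.7 percentage points.

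**5. Bias, type I error and chance imbalance.** Even at λ = 0.05, the actual spread of the estimates hardly depends on adjustment (0.0849 without, 0.0835 with). With no true effect, the 97.5% interval without locality missed zero in 3.2% of trials at λ = 0, 2.2% at 0.02 and 1.8% at 0.05, so locality variance makes the test more conservative. The 3.2% at λ = 0, and coverage of 96.6% to 97.3% with locality in the model, are consistent with using a normal critical value with only 15 PICs. That is a separate matter from locality.

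**6. What λ means in SF12 points.** A difference of 3 points at effect size 0.30 implies an SD of 10. The between-locality SD is 10√λ, and the expected range over four localities is about 2.06 times that: 1.5 points at λ = 0.005, 2.1 at 0.01, 2.9 at 0.02 and 4.6 at 0.05.

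**The case against.** The strongest reply is that this is an omission, and one that an analysis plan normally fills. The article leaves the participant-level covariates unlisted, each participant's locality could be entered among them, and nothing stated is wrong or contradictory. That stands as far as it goes: the point is an improvement to confirm, not an error found.

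Size is the second reply. Practice deprivation index is already an area-linked term in the model, and the residual differences needed for a material effect are large. At λ = 0.02 the expected range of 2.9 points, after adjustment, is close to the trial's own 3-point minimum important difference. The simulation has no covariates, so its figures are upper values for a given crude locality variance. If the planned 0.03 already contains locality, the loss is smaller still. Splitting 0.03 equally between locality and PIC (16 PICs, 1002 analysed, 3000 runs) gave SE 0.0805 against 0.0761 and power 94.2% against 95.8%, both above the planned 90%. All of this stands and limits the claim.

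A reader might also infer three stronger things that the article does not support:

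- **That leaving locality out of minimisation is the fault.** It is not. Chance imbalance between localities adds almost nothing to the true standard error; the issue lies in the analysis model.
- **That usual care is known to differ by locality.** The Usual care section says it is unrestricted and given to both arms. It says nothing of local commissioning or of differences between the four localities.
- **That the treatment estimate is biased or the trial underpowered.** Neither follows. There is no bias, and the power loss depends on an assumed variance.

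**Conclusion.** The point holds as a low-cost improvement to the stated model. The extra interval width is nil at λ = 0, about 2-4% at 0.005-0.01 and about 7-8% at 0.02. In SF12 points, the half-width 2.241 × SE × 10 goes from 1.87 to 1.94 at λ = 0.01 and from 1.88 to 2.01 at λ = 0.02. The PIC ICC would be reported as about 0.038 or 0.044 where the true value is 0.03. The row at 0.05 shows the direction only; the article gives no reason to expect so large a residual difference.

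These figures assume a PIC ICC of 0.03 on top of λ, a near-even spread of PICs over the localities, and a locality effect common to both arms. If the treatment effect itself varied by locality, that would be an interaction, which a locality main effect does not remove.

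**What to change.** Pre-specify recruiting locality (Mid-Mersey, Leeds, Bradford, Wakefield) as a fixed effect for both arms in the PCS and MCS models and in the continuous secondary outcome models. Take the adjusted PIC ICC from that model, and say in the report that it may still include practice effects, because teams are matched to single practices where possible. If the analysis plan already includes locality, confirming this is enough. No change to minimisation is needed.

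The cost is one sentence and three degrees of freedom. Locality is known for every participant from the practice. At λ = 0 the simulated interval width was the same with and without the term to within 0.2%, and power differed by no more than Monte Carlo error. The Trial status section puts analysis after follow-up is complete, so the term can be fixed before outcomes are analysed.
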